# Clinical characteristics and prognosis of acute stroke in pregnancy and puerperium (ASPP) patients and their offspring: a retrospective, observational, nationwide, multicenter study protocol

**DOI:** 10.1186/s41016-025-00396-5

**Published:** 2025-06-04

**Keywords:** Acute stroke, Pregnancy, Puerperium, Clinical characteristics, Prognosis, Offspring

## Abstract

**Background:**

Previous studies on the risk factors and prognosis of acute stroke in pregnancy and puerperium (ASPP) mainly used European and American national healthcare databases, lacking detailed patient-level data and precise event timing.

**Aim:**

(1) To identify the risk factors and prognostic factors for ASPP, (2) to assess the risk of recurrent stroke, particularly during subsequent pregnancies, and (3) to evaluate offspring prognosis.

**Design:**

This study is a retrospective, observational, nationwide, multicenter research project planned to include 400 ASPP patients from 36 centers across 22 provinces in China, from 2015 to 2024. ASPP is defined as acute ischemic or hemorrhagic stroke during pregnancy or within 6 weeks postpartum, confirmed by neuroimaging. Two matched groups will be included for comparison: 400 pregnant/puerperal participants without a stroke history and 400 nonpregnant/puerperal participants with a recent stroke, matched by age and/or stroke etiology.

**Methods:**

All participants will be followed up through telephone interviews. The initial follow-up is scheduled to take place between December 2024 and February 2025. The follow-up phase will consist of three rounds, each lasting 3 months and conducted every 3 years. Primary outcomes include unfavorable functional outcomes (*mRS* > 2 or EQ-5D index score < 0.7) at follow-up for Aim 1, recurrent strokes (neuroimaging-confirmed) for Aim 2, and neonatal asphyxia (Apgar scoring) and future development (ASQ-3) of offspring for Aim 3.

**Discussion:**

The ASPP study is the first nationwide multicenter study to systematically evaluate the risk factors, prognosis, and risk of recurrent stroke in ASPP patients, particularly during subsequent pregnancies. This research may offer new insights into the long-term impacts of pregnancy-related stroke.

**Trial registration:**

ClinicalTrials.gov (NCT06527807).

## Background

Acute stroke in pregnancy and puerperium (ASPP) is a rare but serious complication associated with high morbidity and mortality in women of childbearing age. The incidence of pregnancy-associated stroke is estimated at 30 per 100,000 pregnancies and appears to be rising, with an inhospital mortality rate of 4.2% for pregnant women experiencing acute stroke [1–3]. Compared to their nonpregnant counterparts, pregnant women with acute stroke face a higher risk of deterioration and more complex management needs [4]. Regarding the long-term risk of ASPP, women with pregnancy-associated stroke have lower risks of recurrent ischemic stroke and mortality compared to those with strokes unrelated to pregnancy. Furthermore, the risks of recurrent intracerebral hemorrhage and cerebral venous thrombosis do not differ significantly, and recurrent stroke during subsequent pregnancies remains rare [5].

Previous studies have predominantly utilized large-scale national healthcare data and the International Classification of Diseases (Tenth Revision, Clinical Modification) (ICD-10-CM) to examine the incidence rate and risk factors for ASPP [6–8]. Although these population-based studies benefit from larger sample sizes, they often lack detailed data, which hinders a comprehensive exploration of risk factors and the identification of prognostic predictors and range of variables collected, such as laboratory results, neuroimaging characteristics, and management strategies. This limitation hampers the comprehensive exploration of risk factors and the identification of prognostic predictors. As women with ASPP are generally young and likely to achieve good recovery, no long-term follow-up studies have been conducted to assess their long-term functional outcomes. Additionally, it remains to be explored whether ASPP is solely a short-term risk factor that does not affect a woman’s risk of stroke in future pregnancies or throughout her life.

When pregnant women experience acute strokes, the systemic circulatory system may be severely affected, causing significant fluctuations in blood pressure that impact fetal blood flow [9]. These dramatic changes in fetal blood flow can lead to adverse intrauterine effects, such as fetal distress and neonatal asphyxia, potentially resulting in unfavorable outcomes for the offspring, thereby affecting the prognosis of the offspring [10]. However, no study has explored the impact of acute stroke in pregnancy and puerperium on the offspring and their future development. Besides, AMI (acute myocardial infarction) in pregnancy and ASPP may share a common pathophysiological mechanism, where their onset can be predisposed by physiological changes related to a hypercoagulable state, vascular endothelial remodeling, and alterations in insulin and lipid metabolism [11]. Only a few studies have explored the maternal and fetal outcomes of patients with AMI during pregnancy, and no study has assessed the future development of their offspring, mirroring the current research status of ASPP [12]. Therefore, it is important to understand the maternal and neonatal outcomes of these patients.

Establishing a cohort based on patients with ASPP is essential for addressing the aforementioned issues. Due to the rarity of ASPP, obtaining a sufficient sample size necessitates a nationwide, multicenter study. In 2020, the European Stroke Organisation proposed an international, multicenter, prospective cohort study to comprehensively explore ASPP patients [13]. However, no related study results have been reported to date. Moreover, the study protocol did not include the future development of the offspring of ASPP patients. The objectives of the ASPP study are as follows: (1) to explore the risk factors of ASPP and predictors of its prognosis; (2) to evaluate the risk of recurrent strokes, particularly during subsequent pregnancies, in ASPP patients; and (3) to assess the prognosis of offspring of ASPP patients.

## Methods

### Design

This is a retrospective, observational, nationwide, multicenter study divided into three parts. The first part is a case-control study aimed at identifying the risk factors of ASPP and its prognostic predictors. The second part is a cohort study to evaluate the impact of ASPP on the risk of recurrent stroke. The third part is a cohort study to assess the impact of ASPP on the prognosis of their offspring.

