**Fig. 1 Fig1:**
[figure not shown]
The geographical distribution of centers participating in the ASPP study. The ASPP study aims to include 36 territorial or regional centers across 22 provinces in China

ASPP patients and non-ASPP participants from January 2015 to November 2024 will be included (Fig. 2). Table 1 lists the inclusion criteria and exclusion criteria. ASPP patients are defined as those who experience acute stroke events during pregnancy or within 6 weeks postpartum, confirmed by neuroimaging evidence of cerebral infarction or hemorrhage corresponding to their symptoms.

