**• Medication history**
▪ Antihypertensive (if with record the duration of antihypertensive medication use, including pre-pregnancy and during pregnancy, and the types of medications, such as methyldopa, labetalol, amlodipine)
▪ Antiplatelet
▪ Oral contraceptive
• **Stroke evaluation**
▪ Type: Ischemic (thrombotic, embolic) or hemorrhagic (intracerebral, subarachnoid)
▪ Etiology
(1) Ischemic stroke (carotid stenosis, intracranial atherosclerotic stenosis, cardiogenic embolic stroke, arterial dissection, pregnancy-related hypercoagulable state, moyamoya disease)
(2) Hemorrhagic stroke (AVM, IA, pregnancy-related hypercoagulable state)
(3) Other stroke types: Cerebral venous thrombosis, cerebral sinus thrombosis, stroke caused by systemic inflammation, hematological disorders (such as thalassemia, aplastic anemia), arterial dissection (such as carotid dissection), cardiovascular diseases (such as valvular heart disease, embolism due to atrial fibrillation)
▪ Location and size: Anterior or posterior circulation, cortical or subcortical
▪ Diagnostic neuroimaging: CT, CTA, MRI, MRA, DSA, etc.
▪ Cardiac examination: ECG, echocardiography, etc.
• **Pregnancy-/puerperium-associated variables**
▪ Week of gestation and trimester at stroke onset^a^
▪ Gestational hypertension
▪ Preeclampsia/eclampsia
▪ HELLP syndrome
▪ Gestational diabetes
▪ Frequency of previous pregnancy and pregnancy-/puerperium-associated stroke
• **Data on delivery**
▪ Type: Spontaneous vaginal delivery, cesarean section, or prenatal termination (induced abortion or labor)
▪ Week of gestation at delivery
• **Stroke management**
▪ Ischemic stroke
(1) Nonsurgical treatment (if with record dose and duration): anticoagulant (heparin, warfarin), antiplatelet (aspirin, clopidogrel), intravenous thrombolysis (alteplase, tenecteplase), etc.
(2) Surgical treatment: mechanical thrombectomy, etc.
▪ Hemorrhagic stroke
(1) Nonsurgical treatment: Supportive (blood pressure control, intracerebral pressure control), etc.
(2) Surgical treatment: Open surgery (clipping for IA, excision for AVM, hematoma evacuation), endovascular intervention (coiling for IA, embolization for AVM), ventriculopuncture drainage, etc.
▪ Time relationship with terminating the pregnancy (if with surgical treatment): after, before, or during the same period
• **Complications**

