#### Primary outcome

These are the following: For Aim 1, composite unfavorable outcome defined as *mRS* > 2 or EQ-5D index score < 0.7 at follow-up; for Aim 2, recurrent strokes confirmed by neuroimaging; and for Aim 3, the Apgar scores of newborns and results from Ages & Stages Questionnaires, Third Edition (ASQ-3) at follow-up.

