#### Secondary outcome

These are the following: For Aim 1, unfavorable functional outcomes at discharge; for Aim 2, strokes occurring during subsequent pregnancies; and for Aim 3, the occurrence of intrauterine death, stillbirth, or critical illnesses requiring hospitalization in the offspring (see Table 3).

**Table 3 Tab3:** Outcome measures^a^

• **Women**

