##### Assessment process

Assessors will document changes in patients’ functional status during follow-up, including self-reported and observed capabilities in activities of daily living, to accurately evaluate functional outcomes.

Neonatal asphyxia will be assessed using Apgar scores at 1, 5, and 10 min, with scores of 8–10 defined as no asphyxia, 4–7 as mild asphyxia, and 0–3 as severe asphyxia. The assessment will be conducted by healthcare personnel trained specifically in neonatal care to ensure the accuracy and consistency of the scores.

Developmental outcomes for offspring will be assessed using the Ages and Stages Questionnaire, Third Edition (ASQ-3), which is one of the most widely used tools for screening comprehensive developmental status in children aged 1 to 66 months. The ASQ-3 categorizes developmental status into five subdomains: (1) Communication, (2) gross motor, (3) fine motor, (4) problem-solving, and (5) personal-social. Based on scores in each subdomain, results will be classified as “above,” “close to,” or “below” the threshold. The assessment will be conducted by trained assessors to ensure the reliability and accuracy of the results [14].

Recurrent stroke and stroke during subsequent pregnancy are defined as events where women experience a recurrent stroke and a stroke during a subsequent pregnancy, respectively, both confirmed by corresponding medical or insurance records. Intrauterine death or stillbirth is defined as a dead fetus in the uterus at any trimester or the birth of a dead infant after 28 + 1 weeks of gestation. Critical illness is defined as the offspring requiring hospitalization due to a diagnosed disease, including neurological diseases (such as epilepsy and cerebral palsy), cardiovascular diseases (such as congenital heart disease), gastrointestinal diseases (such as necrotizing enterocolitis), respiratory diseases (such as allergic asthma), urological diseases (such as hypospadias), hematological and immunological diseases, and other major disorders.

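### For Apgar-defined asphyxia, intrauterine death and stillbirth, Aim 3 counts strokes after delivery as exposed, so the pooled estimate cannot be read as an effect of stroke on the newborn

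*Protocol article*

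**What the plan says.** All references are to the Protocol article.

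- **Exposure.** The abstract states: "ASPP is defined as acute ischemic or hemorrhagic stroke during pregnancy or within 6 weeks postpartum, confirmed by neuroimaging". The Methods repeat it: "ASPP patients are defined as those who experience acute stroke events during pregnancy or within 6 weeks postpartum". Pregnancy and puerperium form one exposed group.
- **Aim.** Under Design: "The third part is a cohort study to assess the impact of ASPP on the prognosis of their offspring".
- **Primary outcomes.** Under Primary outcome: "for Aim 3, the Apgar scores of newborns and results from Ages & Stages Questionnaires, Third Edition (ASQ-3) at follow-up". On timing, under Assessment process: "Neonatal asphyxia will be assessed using Apgar scores at 1, 5, and 10 min".
- **Secondary outcomes.** Under Secondary outcome: "for Aim 3, the occurrence of intrauterine death, stillbirth, or critical illnesses requiring hospitalization in the offspring".
- **Mechanism.** The Background argues that stroke in a pregnant woman disturbs fetal blood flow, and that such changes "can lead to adverse intrauterine effects, such as fetal distress and neonatal asphyxia".
- **Model.** Statistical analysis enters ASPP as one factor in linear or generalized linear models for delivery outcomes and ASQ-3. Trimester is among the example subgroups; onset before versus after delivery is not named.
- **Timing data.** Table 2 lists "Week of gestation and trimester at stroke onset", with a footnote that defines the three trimesters and the puerperium. It also lists gestational week at delivery and birth date.

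**The concern.** Exposure has to precede outcome for an estimate to be called an impact. For part of the exposed group the order is reversed: the Apgar score has been given, or the fetus has died, before the stroke happens. The article's own mechanism works through the fetal circulation and has no route after delivery.

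Nothing in the article limits these outcomes to strokes before delivery. Any excess of asphyxia or fetal death among women with postpartum stroke must come from a shared cause (preeclampsia, for example) or from a difficult delivery that preceded the stroke. Under the stated aim it would still be reported as an effect of stroke on the child. One of the affected outcomes is primary, and the article says the Apgar and ASQ-3 results will help physicians inform parents.

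**Working it through.** **Step 1: time order, outcome by outcome.**

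| Aim 3 outcome | When it is settled | Can a postpartum stroke precede it? |
|---|---|---|
| Neonatal asphyxia (Apgar) | within 10 minutes of birth | No |
| Intrauterine death, stillbirth | at or before birth | No |
| ASQ-3 development | at follow-up | Yes |
| Later critical illness | after birth | Yes |

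The problem is confined to the first two rows.

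**Step 2: figures in the plan.** There is none to reproduce. Sample size estimates covers parity and stroke recurrence, and gives no event rate, effect size or power for Aim 3. From the article come 400 ASPP cases, 400 pregnant or puerperal controls matched 1:1, and alpha 0.05 (two-sided assumed). The postpartum share f, the control risk and the risk ratios below are assumptions.

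**Step 3: direction of the bias.** With RR_a the risk ratio for antepartum stroke and RR_p the non-causal ratio for postpartum stroke,

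RR_pooled = (1 − f) × RR_a + f × RR_p.

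Take RR_a = 2.0.

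- *No postpartum association (RR_p = 1.0):* f = 0.2 gives 0.8 × 2.0 + 0.2 × 1.0 = 1.8; f = 0.4 gives 1.6; f = 0.6 gives 1.4.
- *Some postpartum association, f = 0.4:* RR_p = 1.5 gives 0.6 × 2.0 + 0.4 × 1.5 = 1.8; RR_p = 2.0 gives 2.0; RR_p = 2.5 gives 2.2.

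The pooled ratio can fall below, equal or exceed the antepartum ratio. The direction is set by RR_p, about which the article says nothing.

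**Step 4: does restricting to antepartum strokes cost power?** Normal-approximation power for two proportions, 400 per group pooled, against 400 × (1 − f) pairs after restriction. Control risk is 5%.

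| Antepartum risk | f | Postpartum risk | Pooled risk | Pooled power | Antepartum pairs | Power |
|---|---|---|---|---|---|---|
| 10% | 0.2 | 5% | 9% | 60% | 320 | 67% |
| 10% | 0.4 | 5% | 8% | 41% | 240 | 55% |
| 10% | 0.6 | 5% | 7% | 22% | 160 | 40% |
| 15% | 0.3 | 5% | 12% | 94.5% | 280 | 97.8% |
| 15% | 0.5 | 5% | 10% | 76.7% | 200 | 91.8% |
| 15% | 0.5 | 10% | 12.5% | 96.5% | 200 | 91.8% |

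Restriction gains power in the first five rows, where postpartum risk equals control risk. In the last row it loses power. The pooled 96.5% there, however, is the chance of rejecting a null hypothesis that is false partly for reasons unrelated to stroke; it is not power for the effect named in the aim.

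**The case against.** The strongest defence has three parts.

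- **The timing data and a trimester subgroup are planned.** The subgroup list is given as examples, so a split at delivery is feasible, and outcome-specific analysis sets may sit in an SAP that is not shown. This stands as to feasibility. But the article does state the exposure, the outcomes, the causal aim and a model with ASPP as one factor, and a subgroup analysis does not change that main contrast.
- **The objective can be read descriptively.** The Background speaks of assessing the prognosis of the offspring of ASPP patients, and a description of all such children would be legitimate. Design and Statistical analysis, however, both speak of the impact of ASPP.
- **Much of Aim 3 is unaffected.** This stands in full for ASQ-3 and later critical illness.

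Three stronger readings are tempting, and the documents do not support them.

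- *The effect is diluted.* That needs postpartum-stroke risk to equal control risk, which nothing in the article establishes.
- *Restriction gains power.* This rests on the same assumption and reverses in the last row of the power table.
- *Controls have already survived the risk period for fetal loss, because they are not matched on gestational week.* Table 1 asks only that a woman be pregnant or within 6 weeks postpartum. It does not require a live birth, and Table 2 allows prenatal termination as a delivery type. The article does not say how a control's index date is set, so this bias cannot be shown from the text.

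**Conclusion.** The point holds for Apgar-defined neonatal asphyxia, intrauterine death and stillbirth, and only for these. As the article is written, the Aim 3 estimate for them mixes a contrast that could reflect an effect of stroke with one that cannot, so it is not interpretable as the impact of stroke on the newborn. That conclusion follows from the definitions alone and needs no assumed rate.

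Neither the direction nor the size of the bias can be stated. On the assumptions above (antepartum risk ratio 2.0, 40% postpartum strokes), the pooled ratio ranges from 1.6 to 2.2 as the postpartum ratio goes from 1.0 to 2.5. The real postpartum share and asphyxia rates are not in the article.

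**What to change.** For Apgar-defined asphyxia, intrauterine death and stillbirth:

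- Make the primary exposed group strokes with onset before delivery, with their 1:1 matched controls. For fetal death, require onset before the death.
- Alternatively, keep all cases and model antepartum and postpartum onset as separate exposure levels, with the antepartum coefficient as the primary estimate.
- Report postpartum-onset strokes separately, labelled as an association that cannot be causal.

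For ASQ-3 and later critical illness, keep all ASPP cases and report by onset period.

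**Cost.** This is a change of wording in the Aim 3 outcome and analysis text. Onset week and trimester, gestational week at delivery and birth date are already to be collected. Table 2 does not list a date of fetal death, so the order of stroke and death may have to be taken from the hospital record. The price is fewer cases for the birth outcomes, and possibly a lower chance of a significant result if postpartum stroke is associated with them. Re-selecting controls by gestational week would be a much larger redesign and is not needed for this repair.

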### Participating centers and patient population

This study is based on the method of stratified selection of centers according to the “China Maternal and Child Health Development Report (2019).” This study plans to include 36 regional or subregional centers in 22 provinces of China that meet 3 criteria to ensure sufficient geographical representativeness, making it a national-level study. The 3 criteria are the incidence rate of ASPP (> 5 cases per 100,000 pregnancies), the minimum annual case volume (≥ 15 ASPP cases), and obtaining standardized stroke care certification. The distribution of the final cohort of 36 tertiary hospitals is strategic and can reflect geographical and socio-economic diversity. Sample allocation uses adaptive quota sampling and is adjusted quarterly. The enrollment targets of each center are dynamically redistributed according to the real-time recruitment rate to maintain balance among the centers. All the above centers were selected based on voluntary participation. The geographical distribution of centers participating in the ASPP study is illustrated in Fig. 1.

**Fig. 1 Fig1:**
[figure not shown]
The geographical distribution of centers participating in the ASPP study. The ASPP study aims to include 36 territorial or regional centers across 22 provinces in China

ASPP patients and non-ASPP participants from January 2015 to November 2024 will be included (Fig. 2). Table 1 lists the inclusion criteria and exclusion criteria. ASPP patients are defined as those who experience acute stroke events during pregnancy or within 6 weeks postpartum, confirmed by neuroimaging evidence of cerebral infarction or hemorrhage corresponding to their symptoms.

**Fig. 2 Fig2:**
[figure not shown]
Study design flowchart of the ASPP cohort

**Table 1 Tab1:** Inclusion and exclusion criteria

**Inclusion criteria** (1) Aged ≥ 18 years (2) Who are pregnant or within 6 weeks postpartum (3) Patients, their legally acceptable representatives, or relatives who agree to collect personal information for this study and sign an online written informed consent **Exclusion criteria** (1) Missing critical baseline demographic, clinical, or neuroimaging data The key data includes the following: • Age • Body mass index (BMI) • Preexisting conditions (such as a history of hypertension, diabetes, and other chronic diseases) • History of previous strokes • Neuroimaging results (such as CT or MRI findings) (2) Whose offspring have congenital malformations or inborn errors of metabolism (3) With complications affecting cerebral blood flow, such as amniotic fluid embolism during pregnancy (4) The patients’ family members (excluding parents and siblings) have a history of severe mental illness, such as intellectual disability and schizophrenia. In addition, autism spectrum disorder (ASD) is considered a neurodevelopmental disorder, distinct from the traditional definition of mental illness; therefore, it is not included in the exclusion criteria for a family history of severe mental illness (5) Who undergo AMI during pregnancy (6) Who experience non-spontaneous stroke events due to other causes, such as cerebral infarction or hemorrhage caused by surgery	

Grouping of non-ASPP participants is as follows:Non-ASPP participants include two matched control groups: The first group consists of participants in the pregnancy or postpartum period without a history of stroke (pregnancy/postpartum non-stroke group); the second group consists of nonpregnant or non-postpartum participants who have recently experienced a stroke (nonpregnant stroke group).Matching criteriaFor the pregnancy/postpartum non-stroke group, controls will be matched to ASPP cases in a 1:1 ratio based on age (±2 years) and hypertension history, with the latter stratified into preexisting hypertension, pregnancy-induced hypertension, or no hypertension.For the nonpregnant stroke group, a 1:1 matching strategy will be applied using age (±2 years), stroke etiology (classified by TOAST criteria), and preexisting hypertension status.Classification of pregnancy-related etiologies is as follows:Postpartum vascular diseasePregnancy-related hypercoagulable statesPregnancy-induced hypertensionPreeclampsiaAmniotic fluid embolismMatching of nonpregnant/postpartum patientsAge matching (±2 years)Matching based on stroke etiology, such as cardiogenic stroke, atherosclerotic stroke, small vessel disease stroke, and other identifiable causes (e.g., intracerebral hemorrhage)Health status and comorbidities, including common comorbidities such as cardiovascular disease, hypertension, and diabetesLifestyle factors, such as smoking and alcohol consumption historyDiscussion of the impact of pregnancy-related etiologiesEtiological characteristics, such as thrombosis resulting from pregnancy-related hypercoagulable states, hemodynamic changes caused by postpartum vascular disease, and hypertensive lesions associated with preeclampsiaPhysiological changes: Physiological changes during pregnancy, such as increased blood volume, blood pressure fluctuations, and alterations in coagulation mechanismsPsychological and social factors: Assessing the unique challenges faced by pregnant women in coping with stress, anxiety, and other mental health issues, as well as their potential impact on stroke occurrenceImpact assessment: When comparing ASPP patients with nonpregnant stroke patients, the influence of pregnancy-related etiologies on stroke recurrence rates and long-term prognosis will be clearly delineated.

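### Exclusion criterion 2 rules out offspring with congenital malformations, yet two such malformations are named as events of the Aim 3 critical-illness outcome

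*Protocol article*

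**What the plan says.** Under Methods, Participating centers and patient population, Table 1 gives one list of exclusion criteria. Criterion 2 excludes women "Whose offspring have congenital malformations or inborn errors of metabolism". Criterion 4 concerns women whose "family members (excluding parents and siblings) have a history of severe mental illness, such as intellectual disability and schizophrenia". Autism spectrum disorder is the only exemption from criterion 4: "therefore, it is not included in the exclusion criteria for a family history of severe mental illness".

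The Design section describes the offspring part as follows: "The third part is a cohort study to assess the impact of ASPP on the prognosis of their offspring". Its primary outcomes are, "for Aim 3, the Apgar scores of newborns and results from Ages & Stages Questionnaires, Third Edition (ASQ-3) at follow-up". Its secondary outcomes are, "for Aim 3, the occurrence of intrauterine death, stillbirth, or critical illnesses requiring hospitalization in the offspring".

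The Assessment process section defines critical illness as hospitalization of the child for a diagnosed disease. It lists disease categories with examples in parentheses, among them "cardiovascular diseases (such as congenital heart disease" and "urological diseases (such as hypospadias". Table 3, footnote e, lists the same categories without the examples.

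**The concern.** Congenital heart disease and hypospadias are congenital malformations. A center that applies Table 1 removes the mother and child before either condition can be recorded. A center that works from the outcome definition records the same child as having an event. With 36 centers planned, both readings could be in use at once.

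Two further consequences follow from the way criterion 2 is placed.

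- **Timing.** It is an eligibility rule that looks at the child, and eligibility is judged retrospectively on pregnancies going back to 2015. A diagnosis made well after birth can decide whether a woman is in the study.
- **Scope.** It acts on the woman, not on an analysis of her child. As written she is lost to the work on risk factors and functional outcome (Aim 1) and on recurrent stroke (Aim 2).

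At stake are an Aim 3 outcome that cannot be carried out as defined, and avoidable loss of cases of a rare condition in the two maternal aims.

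**Working it through.** No arithmetic applies beyond a count. The article gives no offspring event rate, malformation rate or Aim 3 sample size; its Sample size estimates section covers parity-related stroke risk and stroke recurrence only. The check sets the eligibility rule beside the outcome definition.

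**Step 1. Each disease named under critical illness, against criterion 2**

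| Category | Named example | Congenital malformation? | Countable in an eligible pair? |
|---|---|---|---|
| Neurological | Epilepsy | Not as such | Yes |
| Neurological | Cerebral palsy | Not as such | Yes |
| Cardiovascular | Congenital heart disease | Yes | No |
| Gastrointestinal | Necrotizing enterocolitis | No | Yes |
| Respiratory | Allergic asthma | No | Yes |
| Urological | Hypospadias | Yes | No |

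Two of six named diseases have a count of zero by rule, and 6 − 2 = 4 remain observable. The two further categories (hematological and immunological; other major disorders) carry no example. No inborn error of metabolism is named as an event.

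**Step 2. Does anything in the text limit criterion 2?** Three limits would remove or soften the conflict:

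- a limit to malformations known before the stroke or at birth;
- a limit to earlier children;
- a limit to particular analyses or aims.

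None is stated in Table 1, in the text around it, or in the outcome sections.

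**Step 3. When can the excluding diagnosis be made?** Participants date from January 2015 to November 2024, and the first telephone follow-up runs from December 2024 to February 2025. A child born early in the window could be almost ten years old when eligibility is judged, and one born at its end only weeks old. The chance that a malformation has come to light by then therefore differs with birth year.

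**Step 4. Which outcomes lose events, and which lose children?** Only part of one secondary outcome loses events by definition. However, a child removed under criterion 2 also leaves the Apgar and ASQ-3 comparisons, and a fetal death or stillbirth with a malformation leaves that secondary outcome. These are changes in who is analyzed; the outcomes themselves remain observable.

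**Step 5. Criterion 4.** The parenthesis sets aside parents and siblings only. The woman's child is neither, so the wording does not keep the index child out of the family members who count. Intellectual disability, which the criterion names, overlaps with what the ASQ-3 screens. But the same criterion describes itself as a rule about family history, which ordinarily refers to relatives and not to the child under study. The text is ambiguous.

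**The case against.** The strongest defence is that the exclusion is sensible and the examples are loose drafting. Malformations and metabolic disorders are competing causes of poor development. A stroke after delivery, which the definition of ASPP includes, cannot have caused a malformation. The Background attributes harm to disturbed fetal blood flow leading to distress and asphyxia, not to malformation. On this view, deleting two parenthetical examples settles the matter. Much of this stands: restricting the ASQ-3 comparison in this way is defensible, and the deletion would cure the contradiction. It does not explain why two malformations are named as events, and it does not justify removing the mother from Aims 1 and 2.

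Several stronger readings are tempting, and the document does not support them.

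- **Aim 3 removes its own adverse outcomes.** Only two examples within one component of a secondary outcome are affected as events. Apgar, ASQ-3, fetal death and stillbirth are still measured.
- **Some categories of critical illness cannot occur.** The two conditions are examples. Acquired cardiovascular or urological disease would still count, so all seven categories remain possible.
- **The comparison is biased toward no harm.** If the rule is applied alike to ASPP and comparison offspring, that needs malformations to be more frequent after ASPP, which the article nowhere says.
- **The recurrence comparison is biased because nonpregnant controls have no index child.** Loss on one side narrows the ASPP population. It biases recurrence only if the child's malformation is related to the mother's recurrence risk, and the article gives no ground for that.
- **A number of women lost can be stated.** The article gives no malformation rate, and 400 is the planned number after eligibility, so a rate times 400 does not give the loss.
- **Criterion 4 removes poor ASQ-3 results.** That treats an ambiguous phrase as an operating rule.

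The design flowchart (Fig. 2) is not reproduced in the text available. Table 1 also cannot apply uniformly, since its requirement of pregnancy or recent delivery cannot hold for the nonpregnant stroke group. The reading that criterion 2 acts on all three aims therefore rests on Table 1 as worded.

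**Conclusion.** The contradiction is real and stands in the current text. Criterion 2 and the critical-illness definition cannot both be followed for two of the six diseases named. Either those events are zero by rule or centers will treat like children differently. Eligibility can also depend on offspring diagnoses made after birth, and as written the woman is dropped from two aims for a reason the article does not connect to them.

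The conclusion rests on two points: that congenital heart disease and hypospadias are congenital malformations, and that Table 1 means what it says. It needs no outside rate. Neither the direction nor the size of any bias can be derived, and no primary outcome is shown to be compromised. Criterion 4 calls for a clarification only. Severity: should-fix.

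**What to change.** Reconcile Table 1 with the critical-illness definition in one of two ways.

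1. **Preferred.** Take criterion 2 out of study-level eligibility. Keep these women in Aims 1 and 2, and keep their offspring in the critical-illness and fetal-death outcomes. Apply the malformation and metabolic restriction only to the analysis set for ASQ-3 and, if wanted, Apgar. Report the number restricted in each group.
2. **Alternative.** Keep criterion 2 and remove congenital malformations, including the two named examples, from the critical-illness definition. This cures the contradiction, but it leaves eligibility dependent on later diagnoses and still drops the women from Aims 1 and 2.

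Under either option, state in criterion 4 that the index child is not a qualifying family member. Whether the criterion should cover other relatives is a design preference and not part of this point.

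The cost is a wording change to Table 1 and the outcome definition. The preferred option adds the records of women who would otherwise have been excluded, and makes the offspring sample somewhat more heterogeneous. The restricted ASQ-3 set deals with that where it matters most.
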